# Clinical Trial Protocol Summary

Category: Investigator Initiated Trial

Name and symbol of investigational device: Portable vestibular current stimulator ・GVS-100

Development stage (phase): Verification study (phase III)

Prepared on: June 1, 2022

Version No. 16.0

Title:

A randomized, double-blind, placebo-controlled, crossover study to confirm the efficacy and safety of percutaneous noisy galvanic vestibular stimulation to improve severe balance disorder in patients with refractory vestibulopathy

Coordinating Investigator

[name]

Professor, Department of Otorhinolaryngology, Head and Neck Surgery, Nagoya City University Graduate School of Medical Sciences

[name]

[contact] (main)

Mail: [contact]

Clinical Trial Sites

This clinical trial will be conducted at the University of Tokyo Hospital (Department of Otolaryngology and Head and Neck Surgery), Tokyo Teishin Hospital (Department of Otolaryngology), and Nagoya City University Hospital (Department of Otorhinolaryngology, Head and Neck Surgery).

Clinical Trial Duration:

December 2018 to June 2022

(From the acquisition of consent from the first subject to the end of the clinical trial of the last subject)

Objective

The primary objective of this study is to compare the effects of transcutaneous noisy galvanic vestibular stimulation (noisy GVS [Galvanic Vestibular Stimulation]) using a portable vestibular current stimulator for 4 h on patients with severe unsteadiness symptoms based on vestibular disorder and to evaluate the effects of the stimulation on the improvement of body balance function during the stimulation. The secondary objective is to investigate the efficacy of noisy GVS after 4 h of stimulation and the safety of noisy GVS during and after stimulation.

Clinical Trial Design:

This is a multicenter, randomized, double-blind, placebo-controlled, crossover study.

As shown in Figure 1, the subjects whose written consent is obtained and whose eligibility is confirmed by screening are provisionally enrolled. Subsequently, only subjects for whom optimal intensity exist in the optimal intensity study will be enrolled in the main study. The subjects without optimal intensity will be discontinued at this point, and the study will be terminated after confirming safety 2 weeks later.

The subjects enrolled in the study will visit the hospital approximately two weeks after enrolment and will be randomly assigned in a 1:1 ratio to one of two groups: A group where the effect of optimal stimulation by noisy GVS on improving the body balance function is evaluated in ‘Session I’ followed by evaluation of the effect of placebo stimulation in ‘Session II’ (group A), and the group where the evaluation is performed in the reverse order with the effect of placebo stimulation on the body balance function being evaluated in ‘Session I’ followed by the evaluation of the optimal intensity of noisy GVS in ‘Session II’ (group B). A period of at least 7 days will be allowed between this enrolment and Session I.

Each subject will be stimulated with a portable vestibular current stimulator ("optimal stimulation for each subject" or "placebo stimulation") for 4 h to measure the unsteadiness and safety before and during the stimulation. In addition, the safety and efficacy of such stimulation will be evaluated for 3 h after stimulation to confirm all adverse events and incidents. After the evaluation of Session I, a period of approximately 14 days, but at least 7 days, shall be allowed before the evaluation of Session II. At 2 weeks after the end of the evaluation of "Session II" of the treatment stimulation period, the subjects will be interviewed for adverse events.

For safety, all the adverse events and incidents that occur during the use of the stimulator shall be confirmed.

**screening**

**Acquistion of constn**

**Confirmation of eligibili**

**Provisional enrollment**

**Consideration of optimal intensity**

2 weeks later

**Enrollment**

**Yes**

**Session I**

**Session II**

**Two weeks.**

**washout**

**4 h of GVS**

**4 h of placebo stimulation**

**3h later**

**3h later**

**4 h of placebo stimulation**

**3h later**

**4 h of GVS stimulation**

**3h later**

Group A

**Follow-up (tracing) survey**

**Confirmation of safety**

**End**

**No**

Group B

2 weeks later

**Double blind trial**

**Double blind trial**

6 weeks

2 weeks later

Figure 1. Flowchart of the clinical trial

Number of subjects:

A total of 60 patients (50 enrolled in this study, 40 completed) (Group A: 25 cases, Group B: 25 cases)

Study population:

Patients with severe unsteadiness associated with vestibular disorder who meet the following selection criteria and do not meet the exclusion criteria.

- Inclusion criteria:

1. Patients with unilateral or bilateral vestibular disorder on temperature stimulation test with 2 ml of ice water

- Unilateral impairment refers to CP (Canal Paresis) (%)=(healthy maximum slow phase velocity - affected maximal slow phase velocity)/(healthy maximal slow phase velocity + affected maximal slow phase velocity) x100 ≥ 20; bilateral impairment refers to peripheral vestibular disorder with no nystagmus induction or bilateral maximal slow phase velocity < 10 deg/s. In the calculation of CP, the duration of nystagmus may be used instead of maximum slow-phase velocity.

1. Patients with a total trajectory length of at least 180 cm in 60 s on a stabilometer while standing with closed eyes.
2. Patients who have experienced unsteadiness for at least 1 year after the onset of unsteadiness and whose symptoms have persisted for at least 6 months despite rehabilitation therapy.
3. Patients must be between 20 and 85 years of age and severely associated with vestibular disorders. The sex and status of hearing loss are irrelevant.
4. Patients who understand the details of this clinical trial and have given their written informed consent freely and voluntarily prior to participation in this clinical trial

- Exclusion criteria

1. Patients with metal in their body, such as cerebral artery clips, cochlear implants, or pacemakers (silver teeth are acceptable)
2. Patients with orthopedic diseases, such as fractures, sprains, separated flesh, etc., or patients with acute painful diseases, etc.
3. Patients with limb movement disorders due to cerebellar disorders or spinal cord disease
4. Patients with significant cardiac disease, including severe arrhythmias that may require a pacemaker (atrial fibrillation, severe QT prolongation syndrome, severe atrioventricular block (degree II or higher)), or severe heart failure that interferes with walking
5. Patients with malignant tumors
6. Patients with infectious diseases accompanied by fever, malaise, or dizziness
7. Pregnant and postpartum patients
8. Patients who cannot walk independently
9. Patients with skin abnormalities, such as infection or wound at the site of application, or patients with a history of anaphylactic shock or other severe allergies
10. Patients with lack of or limited legal capacity
11. Patients who have participated in another clinical trial (clinical study) within 3 months prior to the date of obtaining consent or who will participate in another clinical trial (clinical study) at the same time as this study
12. Other patients who have been judged to be inappropriate as subjects by the investigator (sub-investigator)

- Criteria for this registration

Patients with optimal intensity by noisy GVS

Clinical trial endpoints and assessments:

Primary endpoint:

The percentage change from baseline in the total trajectory length at all time points immediately after the start of noisy GVS by the investigational device after 30 min, 1 h, 2 h, and 3 h is measured using a Gravicorder G-620 (Anima, Inc.)

Secondary endpoints:

< Efficacy Evaluation>

- The percentage change from baseline in the outer circumference area and RMS (Root Mean Square [square root of the mean square of the distance between the mean position of all center-of-gravity sway and the measured center-of-gravity position]) values at all time points immediately after the start of noisy GVS, and at 30 min, 1 h, 2 h, and 3 h after the start of noisy GVS
- Percent change from the baseline in the total trajectory length, perimeter area, and RMS values at all time points of 4, 5, 6, and 7 h after the start of noisy GVS
- Ambulatory function

Percent change from baseline in the following items immediately after the start noisy GVS, and at 1 h, 2 h, 3 h, 4 h, 5 h, 6 h, and 7 h after the start of noisy GVS

- Dynamic Gait Index (pha) short form score
- Walking speed, stride length, step time, and left-right sway width during a 10-m walk measured using a gait analyzer (Walk-Mate Viewer, WALK-MATE LAB Co.)
- Subjective improvement score

The items below at immediately after the start noisy GVS, and at 1 h, 2 h, 3 h, 4 h, 5 h, 6 h, and 7 h after the start of noisy GVS

- - The subject's own evaluation in 5 steps of "1: improved, 2: slightly improved, 3: unchanged, 4: slightly worsened, and 5: worsened" compared to the state before the stimulation
- Quality of Life (QOL)

Change from baseline in the items below at 3 and 7 h after the start of noisy GVS

- - Japanese version of the modified Fall Efficacy Scale (mFES) (Appendix 2)
  - Japanese version of the Dizziness Handicap Inventory (DHI) (Appendix 3)
- Activity level

Activity (number of steps walked) immediately after the start of noisy GVS to 3 and 7 h after the start of noisy GVS

< Safety Evaluation>

Evaluate the occurrence of adverse events and defects.

# Definitions of abbreviations and terms

| BMI | Body-Mass Index |
| --- | --- |
| GCP | Good Clinical Practice (Standards for the Conduct of Clinical Trials of Medical Devices) |
| GVS | Galvanic Vestibular Stimulation |
| LED | Light Emitting Diode |
| RMS | Root Mean Square (square root of the mean of the squares of the distances between the mean position of the total center of gravity sway and the measured center-of-gravity position) |
| DGI | Dynamic Gait Index |
| DHI | Dizziness Handicap Inventory |
| FAS | Full Analysis Set (largest analysis population) |
| mFES | modified Fall Efficacy Scale |
| PPS | Per Protocol Set (analysis population that conforms to the study protocol) |
| SAS | Safety Analysis Set |

#

# Introduction

## Background and History

1) Epidemiology, pathogenesis, and prognosis of subject diseases

The annual number of deaths due to falls among the elderly in Japan has been increasing every year; additionally, in 2009, the number was approximately 7,300, exceeding the number of deaths due to traffic accidents. Falls and fractures are the main causes of death and becoming bedridden among the elderly, and the prevention of falls has become one of the most important issues for the Health, Labour, and Welfare Administration. In particular, bedridden patients due to fractures are one of the causes of dementia, and the development of effective measures to prevent falls among the elderly is an urgent issue for Japan, which is facing a rapidly aging society.

One of the most common causes of falls in the elderly is dizziness and balance disorder, approximately 40% of which are attributed to peripheral vestibular disorders. It has been reported that the risk of falling in the elderly with dizziness and balance disorders is approximately three times that of the elderly without such disorders. The treatment of vestibular disorders is extremely important in terms of the prevention of falls and fractures in the elderly.

Vestibular disorders are caused by damage to the vestibule in the inner ear, which controls the sense of balance, and the main symptoms are marked dizziness, unsteadiness, and difficulty in walking. Although the disease per se does not have a significant impact on the prognosis of life, it affects the activities of daily living of the patient and significantly impairs the quality of life. Furthermore, as mentioned above, it can increase the risk of falls, especially in the elderly.

The exact number of patients with vestibular disorders is unknown; however, estimates from telephone interviews in Germany report that approximately 8% of adults experience dizziness due to vestibular disorders^1)^. In addition, screening for vestibular disorders in the United States reported that 35% of adults have some form of vestibular disorder, with or without symptoms of dizziness, and a 12-fold increased risk of falling^2)^.

(2) Current treatment methods of the subject diseases and their problems

For dizziness and balance disorders caused by a unilateral peripheral vestibular disorder, it is effective to promote vestibular compensation by rehabilitation. In unilateral vestibular disorders, the phenomenon of vestibular compensation, in which the symptoms of dizziness and balance disorder gradually lessen over time without recovery of vestibular function is known, and is thought to be achieved based on the plasticity of the central nervous system, mainly in the cerebellum and brainstem. In vestibular rehabilitation, the vestibular compensation is promoted by actively moving the body and providing effective stimulation to the vestibular, oculomotor, and deep sensory systems involved in body balance, thereby improving the symptoms of dizziness and dynamic state of equilibrium disorders. Although this vestibular rehabilitation can improve balance disorders to some extent, it does not necessarily eliminate dizziness and balance disorders completely. There are also a small number of cases of unilateral vestibular disorders in which vestibular rehabilitation is not effective and dizziness and balance disorder remain permanently.

In addition, vestibular rehabilitation is not effective for bilateral peripheral vestibular disorders, and there is no effective treatment for these disorders. Although vestibular regeneration has been investigated as a potential fundamental treatment, it is still in the research stage and has not yet been applied clinically. Moreover, as a treatment for refractory bilateral vestibular disorders, an artificial vestibule that replaces the vestibular function by inserting stimulating electrodes into the three semicircular canals and directly stimulating the nerves electrically in the semicircular canals is being developed in Europe and the United States. However, no clinical trials have been reported and evidence as a treatment method has not been established. In addition, this treatment is also surgically invasive, and the implantation of electrodes into the semi-circular canal may cause hearing loss and worsen the vestibular disorder. Furthermore, the cost of this treatment is high. Therefore, the development of a safer and simpler treatment method is strongly desired.

(3) Principles and benefits of the treatment method

Galvanic vestibular stimulation (GVS) is a method of electrical current stimulation of the vestibular nerve and is conventionally used in actual clinical practice to test the vestibular function. Noisy GVS is a method in which the current used for vestibular stimulation is a weak noisy current. Recently, the stochastic resonance phenomenon, in which a nonlinear response to a weak input signal is reinforced by noise^3）^(Fig. 2), has attracted attention, and its principle has been elucidated^4）^, suggesting that noisy GVS is related to this stochastic resonance phenomenon. Furthermore, it has been shown that noisy GVS, which is weak enough not to cause side effects, such as pain or discomfort, is effective in improving the autonomic reflexes and performance in neurodegenerative diseases, such as Parkinson's disease. Portable noisy GVS has various advantages, such as no surgical invasion, low cost; additionally, the patient does not feel stimulation during use because the balance disorder is treated by applying a surface electrode to the back of the patient's ear and applying a weak current using a small stimulator. If noisy GVS can be shown to be effective in treating refractory peripheral vestibular disorders, it will be possible to treat a large number of patients suffering from dizziness and balance disorders using a simple, non-surgical method.

Threshold

Fig. 2. Principle of stochastic resonance

A nonlinearity signal response is reinforced by providing noise of appropriate magnitude.

(Left) Signals below the threshold bring no information. (Center) When noise of an appropriate magnitude is provided, signals above the threshold appear and the information is increased. (Right) When a larger signal is provided, the information decreases.

## Non-clinical study summary

### Mechanical and electrical testing

#### Electrical safety

The electrical safety of the investigational device was conducted by the Japan Quality Assurance Organization in accordance with the requirements of JIS T 0601-1:2017 "Medical electrical equipment Part 1: General requirements for basic safety and basic performance", and it was determined that all the items met the standard and that the electrical safety of the product was sufficiently ensured.

#### Mechanical safety

The mechanical safety of the investigational device was conducted by the Japan Quality Assurance Organization in accordance with the requirements of JIS T 0601-1:2017 "Medical electrical equipment Part 1: General requirements for basic safety and basic performance", and it was determined that all items met the standard and that the mechanical safety of the product was sufficiently ensured.

#### Electromagnetic compatibility

The electromagnetic compatibility of the investigational device was verified by the Japan Quality Assurance Organization (JQA) in accordance with the requirements of JIS T 0601-1-2:2012 "Part 1-2: General requirements for safety of electrical equipment for medical use - Electromagnetic compatibility - Requirements and tests, and it was determined that all the items met the standard and that electromagnetic compatibility of the product was sufficiently ensured".

#### Specific requirements for basic safety and basic performance of nerve and muscle stimulators

The basic safety and basic performance of the nerve and muscle stimulators for this experimental device was conducted by the Japan Quality Assurance Organization in accordance with the requirements of JIS T 0601-2-10:2015 "Medical electrical equipment Part 2-10: Individual requirements for basic safety and basic performance of nerve and muscle stimulators". It was determined that all the items met the standard and that the individual requirements were judged to be sufficiently secured.

### Biological Safety Assessment

In this experimental device, the device in contact with the human body is an electrode.

Since this electrode is an approved product, no new biological safety evaluation was conducted at this time.

## Clinical Trial Summary

### Results of Investigator-Initiated Clinical Trials 1 and 2

#### Effects of Short-Term Stimulation

The effects of noisy GVS on body balance in the standing position were examined in 21 normal adults and 11 patients with bilateral vestibular disorders. Noisy GVS improved the body balance in 76% of normal subjects and 91% of patients with bilateral vestibular disorders when compared with no stimulation at 80% of the sensory threshold. The improvement in body balance by noisy GVS was greater in patients with bilateral vestibular impairment than in normal subjects5^）^(Figure 3).

A. Electrodes were affixed to the posterior part of the ear and the patient stood on the gravimeter for 30 s with closed eyes while noisy GVS was applied.

B. Effect of noisy GVS in a case of bilateral vestibular disorder (mitochondrial encephalomyopathy). Notably, 400 μA of noisy GVS markedly improved the balance disorder.

**Fig. 3. Effect of noisy GVS on the improvement of balance in patients with bilateral vestibular disorders**

#### Sustained stimulation effect

We conducted an investigator-initiated clinical trial to investigate the effects of sustained stimulation in healthy elderly subjects in 2014.

The results showed that the noisy GVS for 30 min had a lasting effect for 3 h after the end of stimulation^6)^.

### Safety

#### Safety of Investigator-Initiated Clinical Trial 1

Noisy GVS was performed for 30 s using the GVS-100 in normal subjects and patients with bilateral vestibular disorders, and no adverse events were observed during or after stimulation5^)^.

#### Safety of an Investigator-initiated Clinical Study 2

In an investigator-initiated clinical study in healthy subjects, noisy GVS long-term stimulation (30-min and 3-h stimulation) was performed using GVS-100, and no adverse events were observed during or after stimulation^7)^.

## Results of an Investigator-initiated Clinical Study 3^8)^

From October 2016 to January 2017, we conducted an exploratory clinical trial in 13 patients with bilateral vestibular disorders at our hospital to examine the safety of long-term 30-min percutaneous noisy GVS, the carryover effect after the end of stimulation, and whether the optimal stimulation intensity varied twice with an interval of 2 weeks. In Session I, only the optimal intensity was examined, and in Session II and III, the safety and carryover effects of long-term noisy GVS were examined.

### Carryover effects after the end of percutaneous noisy GVS

In patients with bilateral peripheral vestibular disorders, the total trajectory length was significantly improved from baseline at 3 h after stimulation with 30 min of noisy GVS (total trajectory length change in Session II: Fig. 4). A test of contrast comparing the mean values after noisy GVS with baseline values in a mixed-effects model showed that, on average, there was a significant improvement in the total trajectory length up to 6 h after the end of stimulation in both Session II and III (Table 1). In addition, the subjective degree of improvement measured on a 5-point scale also showed a trend toward improvement (Fig. 5). The degree of subjective improvement was correlated with the total trajectory length, suggesting the clinical significance of the total trajectory length.

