# Clinical Trial Endpoints

## Primary endpoint

The percentage change from baseline in the total trajectory length at all time points immediately after the start, after 30 min, 1 h, 2 h, and 3 h of noisy GVS by the investigational device measured using a Gravicorder G-620 (Anima, Inc.)

[Primary endpoint]

The difference between the mean rate of change in the total trajectory length from immediately after the start of stimulation to 3 h after stimulation in the GVS period and the mean rate of change in the total trajectory length from immediately after the start of stimulation to 3 h after stimulation in the placebo period is compared.

[Rational for the setting]

The correlation coefficient between the mean change in the total trajectory length up to 3 h measured in the investigator-initiated clinical trial and the total subjective improvement score (possible range [-10, 10], with higher scores indicating subjective improvement) was -0.60 (*P* = 0.032), suggesting the clinical utility of the total trajectory length. Because total trajectory length was measured at 5 time points (immediately after the start, after 30 min, 1 h, 2 h, and 3 h of noisy GVS) during the 4-h noisy GVS in this trial, the percentage change from baseline in total trajectory length at 5 time points was set as the primary endpoint.

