2. With the subjective improvement score during stimulation as the response variable; allocation group, treatment device, and interaction of time point as the explanatory variables; the mixed effect model with individual effect as the random effect is applied. The least squares means of the treatment effects throughout the stimulations is determined, and the 95% confidence intervals and *P*-values are calculated. The Kenward–Roger method is used to calculate the degrees of freedom.
3. For the subjective improvement scores in all the time points, the mean value and changes over time in the 95% confidence interval by treatment device and time point are illustrated.

- Analysis of QOL data

1. Descriptive statistics will be calculated for the change from baseline in the mFES score, DHI score, and DHI subscale scores at all time points by allocation group, treatment stimulus period, and time point. Subsequently, the allocation groups will be combined and descriptive statistics will be calculated by treatment device and time point. Regarding the difference in the amount of change within individuals, the descriptive statistics are calculated by time point and a one-sample t-test will be performed to calculate the *P*-value.
2. An analysis of covariance will be performed using the mFES score, DHI score, and DHI subscale scores at 3 and 7 h after the start of stimulation, respectively, as the response variables, and the allocation group, treatment device, and baseline values as the explanatory variables.

- Examination of correlations between endpoints

1. Pearson/Spearman correlation coefficients between the rate of change in total trajectory length at each time point during stimulation and the following variables are calculated for each treatment device.

- Percentage change in gait test endpoints
- Subjective Improvement Score

1. Pearson/Spearman correlation coefficients between the rate of change in total trajectory length and the following variables are calculated for each treatment device at 3 and 7 h after the start of stimulation, respectively.

- mFES Score
- DHI Score
- Scores for each subscale of DHI
- Number of steps
- Calculation of posterior probabilities

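### The planned correlations of sway with felt benefit and gait are single-time-point and per device, and leave the crossover's within-patient GVS-minus-placebo contrast unused

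*Protocol*

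**What the plan says.** Section 3.4 describes Study 3: "we conducted an exploratory clinical trial in 13 patients with bilateral vestibular disorders at our hospital". Noisy GVS was given twice: "in Session II and III, the safety and carryover effects of long-term noisy GVS were examined". No placebo period is described.

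Section 3.4.1 draws the inference: "The degree of subjective improvement was correlated with the total trajectory length, suggesting the clinical significance of the total trajectory length". Section 5.1 uses it to justify the primary endpoint. One variable is the mean sway change over the first 3 h. The other is a summed rating, described as "total subjective improvement score (possible range [-10, 10], with higher scores indicating subjective improvement". Both were therefore aggregated over time. The value reported for their association "was -0.60 (*P* = 0.032), suggesting the clinical utility of the total trajectory length".

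In the present trial, section 5.1 defines the primary comparison as the GVS-period mean minus the placebo-period mean of the percent change in sway length. Section 6.2 justifies the crossover by the removal of between-patient variability.

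The link between sway and the other outcomes is handled in section 12.2.4, under correlations between endpoints. Item 1 covers the gait endpoints and the subjective score. Pearson/Spearman coefficients involving "total trajectory length at each time point during stimulation and the following variables are calculated for each treatment device". Item 2 covers mFES, DHI and step count at 3 h and 7 h, also per device. Neither item uses a time-averaged value or a GVS-minus-placebo difference.

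**The concern.** A correlation across patients within one device mixes two things. One is the question of interest: do patients whose sway improves more on GVS than on placebo also feel more improvement on GVS than on placebo? The other is any stable patient characteristic that moves both measures. Patients who tend to report improvement and also tend to show falling sway readings, for example through practice or regression to the mean, create a correlation that has nothing to do with stimulation. Study 3, with no placebo period described, cannot separate the two. This trial can, because most patients supply both periods, but item 1 does not use the contrast.

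The matter at stake is interpretation. A reader will want to know whether a shorter sway path corresponds to something patients notice. The planned coefficients could look supportive without such a link, and none is designated as the one to read first.

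**Working it through.** **1. Reproduce the protocol's figure.** Inputs: r = -0.60, P = 0.032 (5.1); n = 13 (3.4). Section 5.1 does not name the study, so n = 13 is an inference, which the P value can check.

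t = |r| x sqrt((n - 2)/(1 - r^2)) = 0.60 x sqrt(11/0.64) = 2.49 on 11 df, two-sided P = 0.030. Allowing for rounding of r (0.595 to 0.605):

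| n | P range |
|---|---|
| 12 | 0.037 to 0.041 |
| 13 | 0.0285 to 0.0319 |
| 14 | 0.022 to 0.025 |
| 26 (two sessions each) | 0.001 |

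The stated P fits 13 patients with one value each.

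**2. Precision of that figure.** Fisher z: atanh(0.60) = 0.693; half-width 1.96/sqrt(13 - 3) = 0.620. Limits tanh(0.073) = 0.07 and tanh(1.313) = 0.87, so the 95% CI for r is -0.87 to -0.07.

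**3. What a stable trait does.** Let a shared trait account for a proportion s of the variance of each measure under each device, with no other link. Signs are aligned so that positive means improvement on both. Then:

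- within a device, r = s;
- for GVS minus placebo, the trait cancels and r = 0.

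No document gives s. For s = 0.16, 0.36 and 0.60, r within a device is 0.16, 0.36 and 0.60. A simulation at n = 40 with s = 0.60 gave mean r of 0.597 (GVS), 0.596 (placebo) and -0.001 (differences).

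**4. What a true treatment link does.** Give each measure unit variance, 0.6 of it from traits unrelated between the measures and 0.4 error. Add a common patient-specific GVS effect of SD 0.8 to both. Under GVS, r = 0.64/(1 + 0.64) = 0.39. Under placebo, r = 0. For differences, r = 0.64/(2 x 0.4 + 0.64) = 0.44.

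**5. Single readings against session means.** If r = 0.60 held for five-reading sway means and the correlation between time points is c, replacing the sway mean by one reading multiplies r by sqrt((1 + 4c)/5). Power is by Fisher z at n = 40.

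| c | Source | r | Power |
|---|---|---|---|
| 0.3 | 12.1.2, set as conservative | 0.40 | 73% |
| 0.485 | Table 8, Session II average of 0.49, 0.53, 0.30, 0.62 | 0.46 | 86% |
| 0.775 | Table 8, Session III average of 0.84, 0.74, 0.70, 0.82 | 0.54 | 96% |

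Power at r = 0.60 is 99%. The Table 8 values are correlations with the immediate reading only.

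**6. Number of coefficients in item 1.** Six outcomes (subjective score, DGI, walking speed, stride length, step time, sway width) x 4 shared time points (immediate, 1, 2, 3 h) x 2 devices = 48, or 96 if both Pearson and Spearman are run.

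**7. Why the difference needs adjusting for group.** A period effect enters GVS minus placebo with opposite sign in groups A and B. If it shifts both measures by 0.5 of the within-group SD of the difference (an assumption), the pooled spurious correlation is 0.25/(1 + 0.25) = 0.20. Centring within allocation group removes it.

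**8. Precision of the proposed coefficient.** With 40 completers (12.1.1) and one adjustment variable, the half-width on the z scale is 1.96/sqrt(40 - 4) = 0.327. An r of 0.60 would have a 95% CI of tanh(0.366) to tanh(1.020), that is 0.35 to 0.77.

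**The case against.** The strongest reply is that per-device reporting already exposes the artefact. A trait-driven correlation appears under placebo as well as GVS, while a true treatment link appears mainly under GVS (steps 3 and 4), and under step 4 the paired coefficient is only slightly larger, 0.44 against 0.39. This largely stands. What remains is that no comparison of the two devices' coefficients is planned, and that 48 or 96 single-time-point values with no lead one are a poor vehicle for it.

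Detail may also be left to the statistical analysis plan. That would answer an omission, but here the protocol itself states the form of the analysis.

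Four stronger readings are tempting and not supported:

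- That the endpoint's clinical meaning rests on the 13-patient correlation alone. Section 12.1.2 argues separately from the gap to healthy subjects, which supports the size of effect though not that patients perceive it. Patient benefit is also compared directly between GVS and placebo in the analyses of subjective score, gait and quality of life.
- That item 1 is the trial's formal re-test of the endpoint. The protocol gives it no such purpose and plans no test of these coefficients.
- That single readings sharply weaken the analysis. The fall to 0.40 uses the deliberately conservative 0.3, and Table 8 gives 0.46 to 0.54.
- That one Study 3 session was left out selectively. Section 5.1 does not say which session or average was used, an average over two sessions would fit n = 13 equally well, and the study report is not at hand.

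**Conclusion.** The point holds as a minor, inexpensive improvement to an exploratory analysis. Item 1 correlates across patients, at single time points and within each device, so its coefficients can be non-zero through stable patient traits alone: 0.16 to 0.60 for assumed trait shares of 16% to 60%, against zero for paired differences. The direction follows from the algebra; the size depends on shares that no document gives. The only correlation offered for the endpoint's clinical utility is imprecise (-0.87 to -0.07) and comes from a study of bilateral disease with no placebo period described, whereas this trial also enrols unilateral disease. That no placebo period existed is inferred from section 3.4. The primary estimate, its type I error and its power are unaffected.

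**What to change.** In section 12.2.4, correlations item 1, add one lead coefficient:

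- For each patient, take the GVS-minus-placebo difference in the 0-3 h mean percent change of total trajectory length.
- Take the same difference in mean subjective score over the on-stimulation readings (immediate, 1, 2 and 3 h; the score is not collected at 30 min).
- Correlate the two after centring each within group A and group B, or as a partial correlation given group, and report a 95% CI.
- State the sign that would be supportive. The score here runs from 1 (improved) to 5 (worsened), so the supportive sign is opposite to that in Study 3.

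Do the same for each gait endpoint, and keep the per-time-point, per-device coefficients as descriptive. In section 5.1, give the Study 3 coefficient with its n and confidence interval.

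The cost is a few lines of wording and code on data already collected. Only patients with both sessions contribute (about 40), and influences within a session that affect both measures are not removed.
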